*Hypothesis.* The incidences of influenza, pneumonia, IPD and sepsis are lower in people vaccinated than non-vaccinated over 60 years of age.*Study population.* To quantify the impact of influenza and pneumococcal vaccination on influenza, pneumonia, IPD and sepsis incidence and outcomes, a retrospective database study will be performed including about 300,000 persons ≥60 years, living in Thuringia, who are insured with one of the largest statutory health insurances in Germany (AOK PLUS, insured persons form about 40% of the Thuringian population). The exposed cohort group is expected to consist of about 130,000 patients with pneumococcal and/or influenza vaccination in 2014; the unexposed cohort group are patients without pneumococcal vaccination in 2008–2017 and without influenza vaccination in 2012–2017. The observation period covers the years from 2015 to 2017. The study is partly retrospective (2008–2016) and partly prospective (2017). The study was designed in 2017 and we have commenced in 2017 to acquire the data from 2008 to 2016 which are available from German SHIs with a regular delay of 9–12 months, so that the earliest time a SHI can transfer 2016 data is the end of 2017. Data preparation for statistical analysis has just begun and will not be finished before the end of 2018. As the inclusion of patients of 60 years and above in Thuringia insured with the SHI AOK PLUS practically corresponds to a complete survey, power calculations are not regarded as useful. All routine data collected by health insurances are anonymous.*Outcome measures.* Incidence rates and hospital/ICU admission rates of influenza, invasive pneumococcal diseases, pneumonia and sepsis, as well as in-hospital and long-term mortality will be compared between vaccinated and unvaccinated persons.*Statistical analyses.* Retrospective cohort study using adequate adjustment methods (multiple regression analysis, propensity score matching). The data for analysis will be complete; hence no particular missing data handling is necessary.
*Retrospective study based on health insurance claims data from Associations of Statutory Health Insurance Physicians (ASHIPs).*

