##### Study population

*(The study population is identical to* secondary outcomes, section d.) 300,000 persons ≥60 years, living in Thuringia, who are insured in the AOK PLUS. The exposed cohort group is expected to consist of about 130,000 patients with pneumococcal and/or influenza vaccination in 2014; the unexposed cohort group are patients without pneumococcal vaccination in 2008–2017 and without influenza vaccination in 2012–2017. The observation period covers the years 2015 to 2017. We use real-world claims data to determine resource utilisation and costs across all sectors of medical care. A social health insurance (SHI) perspective is adopted. All routine data collected by health insurances are anonymous.

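### The AOK PLUS unexposed group is defined by vaccination status to the end of follow-up, which builds a spurious mortality benefit into the comparison and leaves the other outcomes open to selection of uncertain direction

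*Protocol article*

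**What the plan says.** The cohort is item d of the secondary outcomes in the Protocol article, the retrospective cohort study on health insurance claims data. Its Study population text describes "a retrospective database study will be performed including about 300,000 persons ≥60 years, living in Thuringia", insured with AOK PLUS. The two groups are set as follows.

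- Exposed: "The exposed cohort group is expected to consist of about 130,000 patients with pneumococcal and/or influenza vaccination in 2014". No condition is placed on 2015 to 2017.
- Unexposed: "the unexposed cohort group are patients without pneumococcal vaccination in 2008–2017 and without influenza vaccination in 2012–2017".
- Follow-up: "The observation period covers the years from 2015 to 2017".

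The outcomes are incidence and hospital or ICU admission for influenza, invasive pneumococcal disease, pneumonia and sepsis, "as well as in-hospital and long-term mortality will be compared between vaccinated and unvaccinated persons". The stated analysis is "Retrospective cohort study using adequate adjustment methods (multiple regression analysis, propensity score matching").

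The Study population section under Tertiary outcomes repeats both group definitions and the window ("The observation period covers the years 2015 to 2017") for healthcare costs and utilisation. The Discussion's list of limitations names confounding by indication and healthy vaccinee bias for these cohort studies. Nothing in the article mentions censoring at later vaccination or time-varying exposure.

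**The concern.** The two groups are built by different rules. Exposed status is settled before follow-up starts. Unexposed status can be settled only when follow-up ends, because the no-vaccination window includes all three outcome years. This is conditioning on future exposure.

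Take two people unvaccinated at the end of 2014. One dies in 2015, can no longer be vaccinated, and stays in the unexposed group as a death. The other lives, is vaccinated in 2016, and is removed together with the person-time survived. Deaths are kept and some survivors are discarded, in one group only.

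The selection takes place after baseline, so covariates measured at baseline cannot undo it, and it would occur even if the groups were exchangeable at baseline. It is therefore a different problem from the two biases that the article acknowledges. At stake are the vaccinated-versus-unvaccinated hypothesis of item d and the whole tertiary outcome. With about 300,000 persons, a biased estimate would also look very precise.

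**Working it through.** The article gives no event count, mortality or effect size for this cohort, so there is no stated figure to reproduce. The check asks what mortality ratio the written definition yields when vaccination has no effect.

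**Inputs from the article.** Exposed fixed in 2014; unexposed require no vaccination to 2017; follow-up of 3 years; mortality is an outcome.

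**Assumptions.** Annual death probability m = 2–5%. Annual probability v = 1–15% of a first vaccination during follow-up among those eligible as unexposed at baseline. The article gives neither.

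**True three-year risk in both groups:** 1 − (1 − m)³. At m = 4% this is 1 − 0.96³ = 11.5%.

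**Retained unexposed group.** It holds those who die unvaccinated (D) and those who survive unvaccinated (S). Its apparent risk is D/(D + S). Two timings were used.

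1. Each year's deaths precede that year's vaccinations. With s = (1 − m)(1 − v): D = m(1 + s + s²), S = s³. At m = 4%, v = 10%: s = 0.864, D = 0.1044, S = 0.6450, so the risk is 0.1044/0.7494 = 13.9%. Risk ratio 11.5/13.9 = 0.83. About 25% of the initially unvaccinated are removed (1 − 0.7494).
2. Both act evenly through the year. With μ = −ln(1 − m), ν = −ln(1 − v), h = μ + ν: D = (μ/h)(1 − e^(−3h)), S = e^(−3h). At the same values: μ = 0.0408, ν = 0.1054, h = 0.1462, D = 0.0991, S = 0.6450, so the risk is 0.0991/0.7441 = 13.3%. Risk ratio 0.87.

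Spurious three-year risk ratio (exposed/unexposed), from m = 2% to m = 5%:

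| Later uptake per year | Deaths first | Evenly through the year |
|---|---|---|
| 1% | 0.981–0.983 | 0.986–0.987 |
| 2% | 0.962–0.965 | 0.971–0.974 |
| 5% | 0.907–0.914 | 0.929–0.934 |
| 10% | 0.817–0.832 | 0.858–0.869 |
| 15% | 0.731–0.753 | 0.787–0.804 |

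The ratio hardly depends on m. It depends on v and on timing within the year. If later vaccination falls mostly in autumn, the answer lies between the columns.

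**With the definition corrected.** Fix status before follow-up and censor at later vaccination. Under even timing, person-time is (1 − e^(−3h))/h, so the unexposed death rate is D divided by that, which equals μ exactly. The mortality rate ratio is 1.000 in every scenario.

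**Non-fatal events.** A simulation with no vaccine effect used a death hazard of 3.5%, later vaccination 10% and event 2% per year, with and without log-normal frailty (SD 1). Under the written definition the event rate ratio was:

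- 1.00 without and 0.99 with frailty, if the event does not influence vaccination;
- 1.15 and 1.13, if the event doubles later vaccination;
- 1.50 and 1.47, if the event quadruples it.

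In the last two cases, patients who fall ill and are then vaccinated leave the unexposed group, so the bias runs against vaccination. With censoring at vaccination the event ratio was 0.99–1.01. Costs and utilisation were not computed.

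**The case against.** **Scope.** A reader might infer that vaccination will look spuriously protective on every outcome. The documents and the calculation do not support that. The stated hypothesis of item d concerns incidence, and for non-fatal events the bias can be nil or reversed. For costs and utilisation the direction was not worked out. Only the mortality claim is one-directional. This objection stands and limits the point.

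**Size.** The baseline pool is people with no pneumococcal vaccination since 2008 and no influenza vaccination since 2012. Such persistent non-vaccinees may take up vaccination at a low rate, and at 1–2% per year the distortion is only 1–4%. The deaths-first timing gives the larger bias of the two. This also stands, which is why a range is given.

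**Inference.** The article does not say in so many words that deaths are retained. But mortality is an outcome and no requirement to survive or stay insured to 2017 is stated, so retention is the natural reading. An article may leave person-time rules to a fuller plan. The group definition, however, is written out twice, and that definition is the problem.

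**A different complaint.** A reader might also object that one influenza vaccination in 2014 labels a person exposed for three years, or that the two vaccines are pooled. That is a separate and debatable choice. Fixing exposure at baseline is a recognised approach, misclassification would ordinarily dilute a real effect, and the article's seasonal treatment of influenza belongs to the analyses of data from the Associations of Statutory Health Insurance Physicians. It is not part of this error.

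**Weight.** This is one of five secondary data sources plus the tertiary outcome. Its window lies almost wholly before the campaign began in September 2017, so it does not estimate the campaign's effect.

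**Conclusion.** The unexposed definition is wrong as written in both places. For mortality it inflates the unexposed risk and creates an apparent vaccine benefit from cohort construction alone. The null risk ratio is about 0.96–0.99 at 1–2% yearly later uptake, 0.91–0.93 at 5%, 0.82–0.87 at 10% and 0.73–0.80 at 15%. These figures rest on an assumed 2–5% annual mortality, later uptake that the article does not report, the timing of vaccination within the year, and deaths being retained. For incidence, admissions, costs and utilisation the comparison is open to the same selection, but its direction cannot be stated in advance. The planned baseline adjustment does not address it, and the acknowledged limitations do not cover it. The primary outcomes do not use this cohort and are unaffected.

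**What to change.** Define both groups only on information available by 31 December 2014. Unexposed would then mean no pneumococcal vaccination in 2008–2014 and no influenza vaccination in 2012–2014. Start follow-up on 1 January 2015 for everyone. Handle vaccination in 2015–2017 either as a time-varying exposure or by censoring at vaccination with inverse-probability-of-censoring weights, because those who take up vaccination later may differ in prognosis. State how deaths and loss of insurance are treated. Apply the same definition to the tertiary economic analysis.

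The cost is re-coding of the cohort flags and a slightly more complex model. No new data are needed, and the article says that data preparation had only just begun. Season-by-season classification of influenza exposure and separate reporting of the two vaccines are optional additions.

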### Implementation and dissemination: Activities

The intervention will be implemented from September to February 2017/18 and 2018/19 (Fig. 1). The intervention will be adapted based upon the evaluation results of the first wave.

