##### Study population

The study population comprises a sample of the statutory health-insured population in Germany (~ 85%, with the remainder mainly being privately insured). Patients will be selected from health insurance claims data. These data are generated by all statutory health insurance physicians for outpatient care and regularly transmitted to their Association of Statutory Health Insurance Physicians (ASHIP) as described previously [64]. A subset of variables including (but not limited to) birth date, sex, district of residence, type and date of administered vaccinations, and diagnosis data is transmitted on a quarterly basis to the Robert Koch-Institute (RKI). The administrative regions of the ASHIPs correspond to the federal states. Data is anonymised and an individual patient identifier is created allowing linkage of all the patient’s medical services to the patient identifier. The data on vaccination status and disease incidence is available for all statutory health insured individuals in Thuringia. In Germany about 85% of the population are statutory health insured. For the purpose of impfen60+ all individuals ≥60 years fulfilling certain inclusion criteria will be included in the cohorts. Retrospective analysis shows that for those ≥60 years, approximately 84% (ca. 560.000 individuals) of the statutory health insured proportion in Germany can be expected to be included per cohort. Hence, power calculation is not regarded as useful.

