##### Statistical analyses

Different methodological approaches will be considered to calculate vaccine uptake before and after the intervention. First, coverage will be calculated as the proportion of patients vaccinated per year (pneumococcus vaccination) or per season (influenza vaccination). The denominator will be taken from the KM6 statistics [65]. Second, vaccine uptake will be calculated among selected patients in a cohort approach [66]. Vaccine uptake will be calculated among those individuals who were < 60 years of age at the beginning of the observation period and turn 60 thereafter (thus have a new indication for the vaccine). For pneumococcus vaccination only, vaccine uptake will also be calculated for at-risk groups who have not been vaccinated in the last 5 years before the respective calendar year of interest and are thus recommended to receive the vaccine.

Vaccine uptake for both influenza and pneumococcus will be analysed by age, district, year/season/month and chronic underlying conditions (based on ICD-10 codes).

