*Hypothesis*. If the vaccination uptake increases considerably, related disease incidences will subsequently decrease.*Study population*. See above under primary outcome, vaccination rate.*Outcome measures*. Disease incidences for influenza and pneumococcal diseases among individuals aged ≥60 and in a to be determined subgroup of individuals before vs. after the intervention (2017 - 2019) will be compared in Thuringia vs. outside Thuringia as a function of vaccination uptake.*Statistical analyses*. The health insurance claims data include ICD-10 codes assigned by the physicians specifically for influenza and pneumococcal diseases and disease-related unspecific clinical syndromes. A number of ICD-10 codes that represent the clinical syndromes acute-respiratory infection and influenza-like illness will be selected. For pneumococcal diseases, ICD-10 codes for community-acquired pneumonia and invasive pneumococcal disease will be selected. The data for analysis will be complete; hence no particular missing data handling is necessary.The ICD-10 codes will undergo a data cleaning procedure so that they represent the specific endpoints most accurately. The disease incidence will be calculated as the proportion of diseased patients per year (pneumococcal disease) or per season (influenza disease, third and fourth quarter of calendar year plus first quarter of the subsequent year). The denominator will be taken from the statistics of statutory health insurances [65]. All routine data collected by health insurances and ASHIPs are anonymous.

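### The influenza disease season in the ASHIP claims study (July to March) opens two months before each campaign wave, which can dilute a relative reduction; April to June belongs to no season

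*Protocol article*

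**What the plan says.** The rule stands in the protocol article under Secondary outcomes, source e (retrospective study on ASHIP claims data), Statistical analyses.

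- Measure: "The disease incidence will be calculated as the proportion of diseased patients per year (pneumococcal disease) or per season".
- Season for influenza: "influenza disease, third and fourth quarter of calendar year plus first quarter of the subsequent year".
- Codes: claims carry influenza-specific codes as well as unspecific syndromes, and "A number of ICD-10 codes that represent the clinical syndromes acute-respiratory infection and influenza-like illness will be selected".
- Safeguard: "The ICD-10 codes will undergo a data cleaning procedure so that they represent the specific endpoints most accurately". No restriction by calendar month or virus circulation is mentioned.
- Comparison: incidences before and after the intervention "will be compared in Thuringia vs. outside Thuringia as a function of vaccination uptake". The hypothesis is that incidence falls after uptake has risen considerably.

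Under Implementation and dissemination: Activities, "The intervention will be implemented from September to February 2017/18 and 2018/19".

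**The concern.** The hypothesis has a time order: uptake rises first, and disease falls afterwards. The disease window does not respect that order. It opens in July, while the wave that is meant to raise uptake opens in September. Illness coded in July or August 2017 therefore counts in the first intervention season although nothing in that wave could have prevented it.

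The measure adds to this. As a proportion of diseased patients, it counts each patient once per season. A patient with a qualifying code in July is already a case, so preventing that patient's influenza in February leaves the numerator unchanged.

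At the other end, a case coded in April to June is counted in no season, and no reason is given.

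At stake is how a small or null result from this source would be read. A real fall in winter illness could look smaller than it was.

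**Working it through.** The article gives no event rate, effect size or power figure for this analysis, and it says that a power calculation is not useful for this population. There is no figure to reproduce. The check has three steps.

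**1. Calendar.** Q3+Q4+Q1 covers months 7 to 12 and 1 to 3. The campaign covers months 9 to 12 and 1 to 2. Months 7 and 8 lie inside the disease season but before the wave. Months 4 to 6 lie in no season.

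**2. Effect of including Q3.** All rates here are assumptions. Let *a* be the risk of a qualifying code in Q3, taken as unaffected by that season's vaccinations. Let *b* be the risk in Q4+Q1, and *r* the true relative reduction in Q4+Q1. With each patient counted once and the two periods independent:

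- P = 1 − (1 − a)(1 − b(1 − r)), and P0 is its value at r = 0
- observed relative reduction ÷ r = (1 − a)b / P0, so the lost share is a / P0
- observed absolute difference ÷ true difference = 1 − a

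The lost share of the relative effect is therefore the share of season cases that have a Q3 code. With total risk a + b of 5% or 30%, Q3 shares of that total of 5% to 30%, and a true risk ratio of 0.90:

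| Q3 share | Observed risk ratio (total 5% / 30%) | Relative reduction kept | Absolute difference kept |
|---|---|---|---|
| 5% | 0.905 / 0.905 | 95.0% / 94.9% | 99.8% / 98.5% |
| 10% | 0.910 / 0.910 | 90.0% / 89.7% | 99.5% / 97.0% |
| 20% | 0.920 / 0.921 | 79.8% / 79.0% | 99.0% / 94.0% |
| 30% | 0.930 / 0.932 | 69.7% / 68.0% | 98.5% / 91.0% |

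Worked cell (total 30%, share 30%):

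- a = 0.09 and b = 0.21, so P0 = 1 − 0.91 × 0.79 = 0.2811.
- With r = 0.10, P = 1 − 0.91 × 0.811 = 0.2620, and the ratio is 0.932.
- The lost share is 0.09 / 0.2811 = 32%.
- The absolute difference is 0.0191 against a true 0.21 × 0.10 = 0.021, so 91% is kept.

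Two assumptions pull in opposite directions. Treating all of Q3 as unaffected overstates the loss, because September is a campaign month. Independence understates it if the same patients tend to be coded repeatedly: the winter risk among patients without a Q3 code is then below *b*, so P0 falls and a / P0 rises.

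With Q3 left out, a = 0 and the full *r* is recovered.

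**3. Effect of omitting Q2.** If late cases share the same relative reduction, leaving them out removes the same fraction from both sides of the ratio, which does not change. The absolute difference loses only their share: for an assumed 5%, 10% or 20%, it keeps 95%, 90% or 80%. Precision falls because fewer cases are counted.

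**The case against.** The other side has a good deal of ground.

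- **Same rule everywhere.** Thuringia and the comparators, before and after, use the same window. This stands: the result is dilution, and the rule cannot by itself create a spurious effect.
- **Codes not yet fixed.** The list is open, a cleaning step is planned, and the article does not say that influenza-specific and syndrome codes are pooled. A reader might infer that every summer cold counts as influenza, and the text does not say so. With influenza-specific codes alone the dilution could be small. The cleaning step, however, concerns codes and sets no limit by month, whereas the season is stated outright.
- **Scale not fixed.** The article compares incidences without choosing a ratio or a difference. A reader might infer that any vaccination effect is attenuated. The arithmetic does not support that, since the absolute difference is much less affected and omitting Q2 leaves a ratio unchanged unless the effect differs in those months.
- **Timing.** A reader might infer that nearly all Q3 diagnoses precede vaccination. September is in Q3 and in the campaign, and no vaccination dates are given. Only July and August demonstrably come before the wave.
- **Shared window.** A reader might also infer that one window serves both vaccination and disease. The vaccination coverage section counts influenza vaccination per season without naming months, so there is no basis for this.
- **Quarterly data.** Quarterly transmission may explain whole-quarter windows. It does not explain the choice of Q3, because the alternatives are whole quarters too.
- **Reach.** This is one of five sources meant to cross-validate each other, and the hospital discharge study also covers influenza without this window. This stands and lowers the weight.

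**Conclusion.** The point holds in limited form. The stated July-to-March season counts at least two pre-campaign months as intervention-season disease, which does not fit the time order of the hypothesis. To the extent that unspecific respiratory codes are used, a relative reduction is diluted towards the null by roughly the Q3 share of season cases: about 5% to 32% of it for assumed shares of 5% to 30%. The absolute difference keeps 91% to 99.8% under the same assumptions. The true size cannot be derived from the article, which gives no rates by quarter; the percentages restate the assumed share and are not estimates for this study. The exclusion of Q2 is a separate, smaller matter of lost cases and precision. Weight is minor to moderate.

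**What to change.** Define the influenza disease season in source e as Q4 plus Q1 of the next year. Add Q4+Q1+Q2 as a sensitivity analysis so that late cases are seen at least once. Apply both windows identically to all regions and all seasons, before and after. The Q3 proportion may be reported separately as a largely pre-campaign comparison period; this is optional. If the sponsor prefers to keep Q3, the article should justify it.

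The cost is one line in the outcome definition and no new data, since the windows remain whole quarters of the same claims. The downside is slightly fewer counted events, including September cases that fall within the campaign.
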